## **Laboratory Samples**

Hospital laboratory can be used to access the following tests. If the hospital laboratory has limitation an outside laboratory with NABL accreditations shall be arranged for sample analysis. The following investigations will be conducted:

- ❖ **FASTING BLOOD SUGAR**
- ❖ **POST PRANDIAL BLOOD SUGAR**
- ❖ **ORAL GLUCOSE TOLERANCE TEST**
- ❖ **HbA1C**
- ❖ **URINE SUGAR**
- ❖ **INVESTIGATION FOR VITAMINS & MINERALS**
- ❖ **INVESTIGATIONS FOR DIABETIC NEPHROPATHY**
- ❖ **INVESTIGATIONS OF DIABETIC CARDIOPATHY**
- ❖ **OTHER TESTING METHODS - CBC, LIPID PROFILE, LFT, RFT, CRP, URINE EXAMINATION etc.**

## **Data Collection**

In addition to the CRFs, individual subject files or subject medical records as well as Sponsor approved source data information will be maintained. These files constitute source data, and it is required that they be signed or initialled and dated by the staff recording the data. Data will be entered into CRFs. The CRFs will be kept current, so that they reflect the latest observations on the subjects enrolled in the study. In this trial CRFs designed will be both paper based and electronic version. The CRFs will be reviewed to verify changes made, reason for change, date of change, and person making changes.

The original signed informed consent form will be available for review at each study visit. All records will be kept in accordance with applicable national laws and regulations. Analytical data from the laboratory will be received and filed along with source documents.

## **Informed Consent**

Fully informed consent will be obtained before any study specific procedures are performed. The content and process of obtaining informed consent must be in accordance with all applicable ethical and regulatory requirements. Informed consent form must be signed by the subject voluntarily. In a situation where a subject is unable to provide consent for him/her, informed consent will be obtained from a Legally Authorized Representative (LAR) / next of kin / legally appointed individual in person in the presence of an impartial witness.

## Screening / Randomization, Visit – Day 0

Subjects must meet the inclusion criteria and have none of the exclusion criteria in order to be eligible for randomization in this study. Subjects who meet all eligibility criteria and have signed informed consent will be included under Baseline study visit. Randomization minimizes systematic bias in the selection and assignment of patients to study therapy and provides justification for inferential statistical methods to be used on data from this study. Once the subject is randomized the sponsor representative or the study Investigator will provide the study staff with a unique randomization number for the subject.

Following assessments must be made at this Baseline visit for each study subject:

- Demographics
- Medical History (all known information regarding the subject's health history/relevant surgeries/interventions, prior to signing the informed consent).
- Vital signs: Body temperature, Pulse – beats per minute (BPM), Blood Pressure (BP) mmHg, Respiratory Rate – breaths per minute
- Concomitant medications
- General Examination -
- Systemic Examination: Examination of Respiratory, Cardiovascular, Nervous, Musculo-skeletal and Integumentary System
- BMI
- Blood will be obtained for following laboratory tests:
  - FBS
  - HBA1C
  - Urine- sugar
  - PPBS
  - OGTT
- Investigation for Vitamins & Minerals, Diabetic Nephropathy, Diabetic Cardiopathy and other investigations like CBC, Lipid Profile, RFT, LFT, CRP, Urine Examinations etc.
- Screening for Diabetic Neuropathy& Retinopathy.

## Short term assessment, Visit – Day 90

Following assessments must be made at this Baseline visit for each study subject:

- Vital signs: Body temperature, Pulse – beats per minute (BPM), Blood Pressure (BP) mmHg, Respirations – breaths per minute
- Concomitant medications
- General Examination

- Systemic Examination: Examination of Respiratory, Cardiovascular, Nervous, Musculo-skeletal and Integumentary System
- BMI
- Blood will be obtained for following laboratory tests:
  - FBS
  - PPBS
  - HBA1C
  - OGTT
  - Urine- sugar
- Investigation for Vitamins & Minerals, Diabetic Nephropathy, Diabetic Cardiopathy and other investigations like CBC, Lipid Profile, RFT, LFT, CRP, Urine Examinations etc.
- Screening for Diabetic Neuropathy & Retinopathy.

#### **Interim assessment, visit – Day 180**

Following assessments must be made at this Baseline visit for each study subject:

- Vital signs: Body temperature, Pulse – beats per minute (BPM), Blood Pressure (BP) mmHg, Respirations – breaths per minute
- Concomitant medications
- General Examination
- Systemic Examination: Examination of Respiratory, Cardiovascular, Nervous, Musculo-skeletal and Integumentary System
- BMI
- Blood will be obtained for following laboratory tests:
  - FBS
  - PPBS
  - HBA1C
  - OGTT
  - Urine- sugar
- Investigation for Vitamins & Minerals, Diabetic Nephropathy, Diabetic Cardiopathy and other investigations like CBC, Lipid Profile, RFT, LFT, CRP, Urine Examinations etc.
- Screening for Diabetic Neuropathy & Retinopathy.

#### **End of treatment/Trial visit (EOT) - Day 730**

Following assessments must be made at this EOT visit for each study subject

- Vital signs: Body temperature, Pulse – beats per minute (BPM), Blood Pressure (BP) mmHg, Respirations – breaths per minute
- Concomitant medications
- General Examination

- Systemic Examination: Examination of Respiratory, Cardiovascular, Nervous, Musculo-skeletal and Integumentary System
- BMI
- Blood will be obtained for following laboratory tests:
  - FBS
  - PPBS
  - HBA1C
  - OGTT
  - Urine- sugar
- Investigation for Vitamins & Minerals, Diabetic Nephropathy, Diabetic Cardiopathy and other investigations like CBC, Lipid Profile, RFT, LFT, CRP, Urine Examinations etc.
- Screening for Diabetic Neuropathy & Retinopathy.

#### **Assessment of effect of trial drug: Day 01 to EOS**

The initial assessment will be done before the commencement of the study (0th day) and simultaneously the study will be initiated. Further assessment will be done on the 3rd month and will be followed on every six months till the completion of the study (i.e. 90th, 180th, 365, 545 & 730thday). Interim data analysis will be done at the end of first six months (180th day) and report will be published.

## Flow chart of the proposed study

[figure not shown]

## Major milestones of the proposed study

[figure not shown]

## **PLAN OF STATISTICAL ANALYSIS**

Appropriate statistical tools will be used for the study.

### **Criteria for Discontinuation from Study Drug or Study Participation**

#### **Withdrawal from receiving study drug**

A subject may remain in the study but discontinue the administration of study drug at any time during treatment. Reasons for this may include:

- ❖ A subject's desire to withdraw for any reason.
- ❖ Intolerable adverse event(s)
- ❖ Subject's request
- ❖ A subject's substantial non-compliance (e.g. visits non-compliance) after agreement with the Sponsor.
- ❖ Investigator's judgment (e.g. related AE)

In any above case of withdrawal or lost to follow-up, the subject's status shall be documented appropriately in the subject source document and will be reported to Sponsor.

### **Safety Assessments and Reporting**

#### **Adverse Events**

An Adverse Event (AE) is defined as any untoward medical occurrence in a subject administered with a pharmaceutical product, which does not necessarily have a causal relationship with this treatment. An AE can therefore, be any unfavourable and unintended sign, symptom, or disease temporarily associated with the use of a medicinal (investigational) product, whether or not considered related to the medicinal (investigational) product.

Examples of adverse events include:

- ❖ Increase in severity of a baseline event
- ❖ Clinically significant worsening of lab values post baseline
- ❖ A new event with an onset date post Baseline

As far as possible, each AE will also be described by:

- ❖ The duration (start and end dates)
- ❖ The severity grade (Grade 1/mild, Grade 2/moderate, Grade 3/severe, Grade 4/Potentially life threatening as defined by the DAIDS Toxicity Table)
- ❖ The relationship to the study drug (none, unlikely, related)
- ❖ Whether the AE involved bleeding of any kind
- ❖ The action(s) taken
- ❖ The outcome

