|                                 | 
given. Placebo for this trial will be given in the similar form as that of the trial drug. Placebo must be consumed according to the same procedures and guidelines as DiabetEaze Powder.
                                                                                                                                                                                                                                                                                                                                                                                                                                                                                                                  |
| CRITERIA FOR EVALUATION: | 
Efficacy:
 
 
• Fasting Blood Sugar
 
• Post Prandial Blood Sugar
 
• Oral Glucose Tolerance Test
 
• HbA1c
 
• Urine Sugar
 
• Investigation for Vitamins & Minerals
 
• Investigations for Diabetic Nephropathy
 
• Investigations for Diabetic Cardiopathy
 
• Investigations for Diabetic Neuropathy
 
• Investigations for Diabetic Retinopathy
 
• Other Laboratory investigations– CBC, Lipid Profile, LFT, RFT, CRP, Urine Examination etc.
 
 
Safety:
 
 
• ADR/AEs using MedDRA
 
• RFT & LFT
 
 |

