### Secondary objectives:

- ❖ Assessment of hypoglycaemic effect of DiabetEaze Powder.
- ❖ Assessment of effect of DiabetEaze Powder in Pre-Diabetes.
- ❖ Assessment of reduction in complications.

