### **Participant recruitment process**

Subjects must meet the inclusion criteria and have none of the exclusion criteria in order to be eligible for randomization in this study. Subjects who meet all eligibility criteria, and have signed informed consent will be included under Baseline study visit. Once the subject is randomized the Sponsor Representative or the Study Investigator will provide the study staff with a unique randomization number for the subject. At the Randomisation, subjects will be centrally, dynamically randomised in a 1:1:1:1:1:1 fashion to each of the following six groups, namely two controls and four trial groups each with 30 subjects.

1. Group 1: Control group for Pre-Diabetes (30 subjects).
2. Group 2: Study group for Pre-Diabetes (30 subjects).
3. Group 3: Control group for Type II DM (30 subjects).
4. Group 4: Study group for Type II DM – Study drug will be administered as add on therapy with Allopathic medicines (30 subjects).
5. Group 5: Study group for Type II DM – Study drug will be administered as add on therapy with AYUSH medicines (30 subjects).
6. Group 6: Study group for Type II DM – Study drug will be administered along with life style management (30 subjects).

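### The adverse-event record singles out bleeding, while hypoglycaemia is neither named as a safety outcome nor asked about uniformly at visits

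*Protocol*

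**What the plan says.** The Adverse Events section of the protocol gives a general definition: "An Adverse Event (AE) is defined as any untoward medical occurrence in a subject administered with a pharmaceutical product". It counts "Clinically significant worsening of lab values post baseline" as an example. Each recorded event is then to be described by duration, severity grade, relationship to study drug, action taken, outcome and one event-specific item: "Whether the AE involved bleeding of any kind".

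The Clinical Trial Summary lists the safety criteria as "ADR/AEs using MedDRA" plus renal and liver function tests. The blood sugar tests, the glucose tolerance test and HbA1c appear there under efficacy only.

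The Secondary objectives include "Assessment of hypoglycaemic effect of DiabetEaze Powder". Under Participant recruitment process, Group 4 is described by "Study drug will be administered as add on therapy with Allopathic medicines", and Group 5 receives the powder in the same way with AYUSH medicines. Each group has 30 subjects. The Reference Therapy entry of the Summary gives standard of care to the study groups generally.

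The Specification of safety parameters section schedules safety reviews on days 90, 180, 365, 545 and 730. It allows extra assessments at discretion and names no trigger for them.

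**The concern.** A trial that looks for a glucose-lowering effect, partly on top of other medicines, has an obvious reason to watch for glucose falling too low. The protocol does single out one type of event in its adverse-event record, but that type has no stated link to the product, the population or any endpoint. The type that does follow from its own objective is left to general reporting.

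At stake is the safety comparison. Mild episodes that resolve between visits are easily forgotten or not mentioned if nobody asks. If asking depends on the staff member or the group, the counts by group cannot be compared with confidence. A statement that the add-on was well tolerated would then rest on incomplete, and possibly unequal, information about the event closest to the intended effect. Data not collected at a visit cannot be recovered in the analysis, so this is a matter for the protocol and not for a statistical analysis plan.

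**Working it through.** The protocol states no figure on this point, so there is none to reproduce. The check sets the sections side by side and works out the visit gaps.

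**1. Where bleeding appears.** Only in the Adverse Events description list. The protocol has no bleeding-related eligibility criterion, no haemostatic endpoint and no stated bleeding risk.

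**2. Where hypoglycaemia appears.**

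| Protocol section | Hypoglycaemia as a harm? |
|---|---|
| Rationale | Yes, once, as an acute complication of diabetes |
| Summary, Criteria for Evaluation (safety) | No |
| Adverse Events | Not named |
| Serious Adverse Events | Not named |
| Specification of safety parameters | No |
| Visit lists, days 0, 90, 180 and 730 | No |

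**3. What the visit lists ask.** The itemised lists cover vital signs, concomitant medications, examinations, BMI, laboratory tests and screening for complications, with demographics and medical history added at day 0. None contains an adverse-event enquiry of any kind. Days 365 and 545 are scheduled but have no itemised list.

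**4. Gaps between safety reviews** (inputs: day 0 and the five review days).

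- 90 − 0 = 90 days
- 180 − 90 = 90 days
- 365 − 180 = 185 days
- 545 − 365 = 180 days
- 730 − 545 = 185 days

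**5. Whether the laboratory schedule fills the gap.** After baseline, glucose tests are itemised at three visits (days 90, 180 and 730). If days 365 and 545 follow the same pattern there are five testing occasions in 730 days. Visit-day values at that spacing cannot show what happened in between.

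**6. Who is exposed.** Groups 4 and 5 together are 30 + 30 = 60 subjects on the powder with other medicines. The argument is weaker for Group 6, described with life-style management, and for Group 2, which is pre-diabetes, although the Summary gives standard of care to all study groups.

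**The case against.** The strongest reply is that existing provisions already cover the event. A reported episode meets the general adverse-event definition and would be coded in MedDRA. A clinically significant low value could count as laboratory worsening. A severe episode would meet the serious-event criteria. All of this stands, so it would be wrong to say that hypoglycaemia is not collected.

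The description list also applies to events already recorded. Replacing the bleeding item with a hypoglycaemia item would not find one more episode. That stands too: the remedy that matters is the question at the visit.

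The protocol excludes insulin users and, in the body list though not in the Summary, subjects with fluctuating blood sugar. It names no background drug class. The objective's wording can simply mean glucose lowering, and the protocol does not rank harms. The exclusions lower the risk but do not remove it, since other glucose-lowering medicines are not excluded.

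Two stronger readings are tempting and unsupported. A reader might infer that episodes enter the data only if a subject volunteers them. The protocol does not say how events are elicited, and the case report form and the flow chart were not available for this check. What can be said is that active questioning is not required. A reader might also infer that everyone knows who takes the powder, because the design is labelled open. The Reference Therapy entry gives controls a placebo of similar form, and the Serious Adverse Events section provides for unblinding. The documents conflict on blinding, so unequal reporting is possible but not established.

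**Conclusion.** The point holds in a limited form. The protocol singles out an event type with no stated relevance. It does not name hypoglycaemia as a safety outcome or require a uniform question about it, despite a glucose-lowering objective and add-on use in Groups 4 and 5. Mild episodes in gaps of 90 to 185 days may be under-counted, and capture may be unequal between groups if allocation is known.

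The under-count cannot be sized from the documents, which give no reporting rate and no expected frequency. A confidence limit for zero events in groups of 30 would not measure it: that limit reflects group size and would be the same with a perfect form. Scaling it by an assumed reporting rate would only return the assumption.

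The conclusion rests on two things: that sites follow the visit lists as written, and that hypoglycaemia is a foreseeable harm. The second is an inference from the protocol's own objective and add-on design. No efficacy estimate is affected. It is worth correcting because the gain in safety data is concrete and the change is small.

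**What to change.** - Add the same hypoglycaemia question for every subject in all six groups to the visit lists for days 0, 90, 180 and 730, and to the reviews on days 365 and 545. Record symptoms, the glucose value if one was measured, and whether assistance was needed.
- Add hypoglycaemia by group to the safety criteria in the Clinical Trial Summary.
- In the Adverse Events section, either state why bleeding is singled out or remove the item.

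The clinical definition of an episode and its management are for the sponsor and investigators to set. The cost is one more case report form item at each visit and one more safety table.

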## **Serious Adverse Events**

Information about all Serious Adverse Events (SAEs) will be collected and recorded on the SAE Report form within 24 hours of learning of its occurrence. A paper SAE form should be completed by the investigators and faxed or emailed to the Sponsor within 24 hours using the safety reporting contact information provided. An SAE is any undesirable sign, symptom, or medical condition which:

- ❖ Is fatal or life-threatening (i.e. an event with an outcome of ‘Death’), or
- ❖ Requires or prolongs inpatient hospitalization, or
- ❖ Results in persistent or significant disability/incapacity, or
- ❖ Is medically significant, as determined by a qualified health professional, may jeopardize the subject, and may require medical or surgical intervention to prevent one of the outcomes listed above
- ❖ Any adverse event causing the need for unblinding will be handled as a serious adverse event.

## **Specification of safety parameters**

For ensuring safety of the subjects, the review on 90th, 180th, 365, 545 & 730th day is scheduled. If found necessary, short-term assessments other than the above stated will be performed. However, in case of emergency conditions between treatments, the trial drug will be discontinued and conditions will be managed accordingly.

## **Provision of auxiliary care**

In the event of a medical emergency, where it is imperative to know which treatment arm the subject was randomized to in order to make future treatment decisions, the Investigator make necessary arrangement for expert management.

## **Medical Monitor Coverage**

Each subject will be provided with contact information of the Principal Investigators. When a subject present to a medical facility where the treating physician or health care provider requires access to a physician who has knowledge of the investigational product and the clinical study protocol and the Principal Investigator is not available, the treating physician or health care provider can contact the Trial Monitor.

## **Changes to the Protocol and Informed Consent Form**

Study procedures will not be changed without the mutual agreement of the Investigators and Sponsor. If there are any substantial changes to the study protocol, then these changes will be documented in a study protocol amendment and if required, in a new version of the study protocol. The amendment is to be approved by the relevant IRB/IEC and if applicable, also

the National Regulatory Authority approval, before implementation. Local requirements are to be followed for revised protocols.

## **DATA MANAGEMENT**

### **Documentation**

Case report forms (CRFs) will identify each subject-by-subject number and subject's initials (per local regulatory guidelines). Originals or copies of all source documents, and correspondence will be kept on file at the investigational site.

The data required by the protocol will be recorded in the appropriate pages of CRFs. All source data will be available to the study monitor who may perform a 100% data check (comparison of the data recorded in the eCRF with those in the source documents). The source data will also be available for an audit by the Sponsor and all applicable regulatory agencies at any time.

### **Subject Data Protection**

The Informed Consent Form (ICF) will incorporate (or, in some cases, be accompanied by a separate document incorporating) wording that complies with relevant data protection and privacy legislation.

### **Storage and maintenance of data**

The Investigator follows the principles outlined in the Clinical Study Agreement on the archival of trial related documents post study. Local IRB procedures and country regulations needs to be followed on archival of documents.

### **Ethics & Good Clinical Practice**

This trial will be carried out in compliance with the protocol and in accordance with all applicable Standard Operating Procedures (SOPs). These will be designed to ensure adherence to GCP, as described in:

ICH Harmonized Tripartite Guidelines for Good Clinical Practice 1996. The Investigator agrees, when signing the protocol, to adhere to the instructions and procedures described in it, and thereby to adhere to the principles of GCP to which it conforms.

### **Institutional Review Board/Independent Ethics Committee**

Before implementing this study, the protocol, the proposed informed consent form and other information to subjects will be reviewed by a properly constituted IEC. A signed and dated statement that the protocol and informed consent have been approved by the IEC will be given to the Sponsor before study initiation. The name and occupation of the Chairman and

the members of the IEC will be supplied to the Sponsor. This committee will approve any amendments to the protocol, other than administrative changes.

### **Audits and Inspections**

Authorized representatives of Sponsor, a regulatory authority, or an IRB/IEC may perform audits or inspections at the centre, including source data verification. The purpose of an audit or inspection is to systematically and independently examine all study-related activities and documents, to determine whether these activities were conducted, and data were recorded, analyzed, and accurately reported according to the protocol, GCP, guidelines of the ICH, and any applicable regulatory requirements. The Investigator will contact Sponsor immediately if contacted by a regulatory agency about an inspection at the site.

